## Abstract

**Background:**

For alcohol drinkers in South Africa it has been found that annual consumption per drinker is among the highest in the world. High prevalence rates of hazardous and harmful alcohol use have also been found in a hospital out-patient setting in South Africa. Hospital settings are a particularly valuable point of contact for the delivery of brief interventions because of the large access to patient populations each year. With this in mind, the primary purpose of this randomized controlled trial is to provide screening for alcohol misuse and to test the efficacy of brief interventions in reducing alcohol intake among hospital out-patients in South Africa.

**Methods/Design:**

The study design for this efficacy study is a randomised controlled trial with 6- and 12-month follow-ups to examine the effects of a brief alcohol intervention to reduce alcohol use by problem drinkers in a hospital setting. The unit of randomisation is the individual out-patient identified as a medium risk drinker attending [name] Hospital. Out-patients will be screened for alcohol problems, and those identified as medium risk drinkers will be randomized into an experimental or control group. The experimental group will receive one brief counselling session on alcohol risk reduction, while the control group will receive a health education leaflet.

**Discussion:**

The trial will evaluate the impact of alcohol screening and brief interventions for patients with alcohol problems in a hospital out-patient setting in South Africa. The findings will impact public health and will enable the health ministry to formulate policy related to brief alcohol interventions, which will result in reduction in alcohol use.

**Trial registration:**

PACTR201110000319392

## Background

Of the 20 countries in Africa identified by the World Health Organisation (WHO) with very high levels of child and adult mortality, it was estimated that for 2000 the total alcohol consumption per adult was 7.1 litres of absolute alcohol [1]. However, when one takes into consideration that a relatively low percentage of adults in these countries including South Africa consume alcohol (55% of men and 30% of women), the annual consumption per drinker increases to 16.6 litres of absolute alcohol, the highest level for any region of the world [1]. In addition, the overall pattern of drinking in the African region in 2000 was ranked as the second most detrimental in the world (indicative of high rates of binge drinking and alcohol dependence) with 1% of all deaths among women and 4% of all deaths among men attributable to alcohol [1,2]. Corresponding figures from South Africa were 10.7% for men and 3.1% for women [3].

In a sample of 1532 (56.4% men and women 43.6%) hospital outpatients in South Africa, 41.2% of men and 18.3% of women were found to be hazardous drinkers, and 3.6% of men and 1.4% of women meet criteria for probable alcohol dependence or harmful drinking as defined by the Alcohol Use Disorder Identification Test (AUDIT) [4]. Strebel, Stacey and Msomi [5] investigated psychiatric hospital patient records (n = 7938) in Cape Town and found that alcohol abuse was prevalent among 6.3% of women and 15.1% of men. Hospital settings are a particularly valuable point of contact for the delivery of brief interventions because of the large access to patient populations each year [6,7]. A number of randomised controlled trials have shown [8] including more recently two trials in non-health care settings in low and middle income countries [9,10] that, in comparison with controls, hazardous and harmful drinkers receiving 5-10 minutes of brief structured advice plus a self-help booklet from health care workers will reduce alcohol consumption by an average of 25%. Overall, it has been estimated that around 20% of patients identified as hazardous or harmful drinkers who receive a brief intervention will reduce their alcohol consumption [11].

The proposed project is a randomized controlled trial aimed at evaluating Screening and Brief Intervention (SBI) for alcohol problems among hospital out-patients in Gauteng province, South Africa.

### Aim of the study

The aim of this study is to assess the effectiveness of Screening and Brief Intervention (SBI) for alcohol problems among hospital out-patients in South Africa using a randomized controlled trial design.

### Objectives

1. To measure the prevalence of alcohol consumption amongst out-patients at [name] Hospital.

2. To describe drinking patterns of out-patients at [name] Hospital, and identify medium risk drinkers needing intervention.

3. To compare level of alcohol consumption amongst medium risk drinkers between pre-intervention, 6 months, and 12 months after intervention among out-patients at [name] Hospital.

4. To compare alcohol consumption between intervention and control groups at 6 and 12 months.

## Methods/Design

### Design

The study design for this efficacy study is a randomised controlled trial with 6- and 12-month follow-ups to examine the effects of a brief alcohol intervention to reduce alcohol use by problem drinkers in a hospital setting. The unit of randomisation is the individual out-patient identified as a medium risk drinker attending [name] Hospital.

### Study population and participants

The sample will include out-patients of [name] Hospital. Out-patients will be screened for alcohol problems, and those identified as medium risk drinkers will be randomized into an experimental or control group. The experimental group will receive one brief counselling session on alcohol risk reduction, while the control group will receive a health education leaflet. The control group will be offered a delayed brief alcohol intervention if the intervention proves to be efficacious.

#### Study hypotheses

• Out-patient medium risk drinkers in the intervention group reduce drinking much more than those in the control group.

• The drinking patterns of patients in the intervention group will continuously reduce over a 12 month assessment period.

### Principles for recruitment

#### Inclusion criteria

Out-patients (males and females) 18 years and above, without mental impairment, who visit the hospital out-patient department and who scored as medium risk drinkers (i.e. 8-19 for men and 7-19 for women on the AUDIT questionnaire) will be included in this study.

#### Exclusion criteria

Out-patients with a score of 20 and above on the AUDIT (with probable alcohol dependence). Also, out-patients who score less than 8 for men and less than 7 for women on the AUDIT questionnaire, patients with mental impairment, those who are pregnant, and those who are already under alcohol treatment, will all be excluded.

### Randomization

After baseline assessment, each patient is randomized to either a control or a brief intervention group. Randomisation is achieved by concealed centrally-allocated computer generated random numbers.

### Blinding

Hospital staff members and out-patients will not be blind to their intervention or delayed intervention status. However, to protect against information biases in the reporting of alcohol use behaviour, the data collection team who will assess the outcomes will be blind to the client's status as intervention or delayed intervention arm.

### Procedure

Universal screening of all presenting out-patients will be used whereby all consecutive clients visiting out-patient departments will be screened for alcohol problems and randomized into an intervention or control group. Research assistant 1 will ask for consent from patients attending the hospital out-patient department to participate in the study, i.e. do a baseline assessment using the AUDIT questionnaire. Research assistant 1 will not be involved in delivering treatment. Research assistant 2 will score the results of the alcohol test section of the questionnaire. Hospital out-patients who score 8-19 for men and 7-19 for women on the AUDIT questionnaire after screening (risky drinkers) will be included in this study. Patients with a score of 20 and above on the AUDIT (with probable alcohol dependence) will be referred for further management. Research assistant 2 implements the randomization to intervention or control arms. Research assistant 2 will carry out the intervention for all the participants, after which they will be followed up at 6 months and 12 months, and assessments will be done by Research assistant 1, who will be blinded to the intervention allocation of the participants. In the event of a drop-out, at least six individual attempts will be made to contact patients by telephone and letter. Even if a contact was not successful at 6 months, further attempts will be made at 12 months. Sampling will occur throughout all hours of clinic operation over a 4-month period. Two-hundred and eighty patients will be recruited from hospital out-patient departments. They will receive 40 South African Rands for transport for returning to the hospital and completing each of the two follow-up assessments (in total R 80). (see Figure 1)

**Figure 1 F1:**
[figure not shown]
**Overview of study activities**.

#### Consent

Consent to participate will be obtained in a 2-stage process. Research assistants will initially ask for informed consent to conduct health screening and collect some basic demographic information and check eligibility to take part. No identifiable information will be collected at this stage. Patients who then are positive on the AUDIT (alcohol medium risk score), as applicable, will have the study explained to them verbally by another research assistant counsellor and in writing (using the patient information leaflet). Informed consent will be obtained at this second stage which will include permission to give the patient's data and contact details to the research staff, and participate in the experimental or control condition and follow up after 6 and 12 months by the research assistant.

### Interventions

#### Control arm

Participants randomized to this group will not receive feedback on the initial alcohol screening. They will be provided with a health education leaflet on responsible drinking, and they will only receive the brief intervention at the 12 month follow-up if the intervention has proved to be efficacious.

### Experimental arm: brief intervention

Participants who are randomized onto the brief intervention arm receive personalized feedback on their AUDIT results, a health education leaflet, simple advice plus brief counselling about reducing excessive drinking, during a one session 20 minute intervention. The steps of brief counselling are: 1) To identify any alcohol-related problems mentioned in the interview, 2) To introduce the sensible drinking leaflet, emphasise the idea of sensible limits, and make sure that patients realize that they are in the medium-risk drinking category, 3) To work through the first 3 sections of the problem solving manual while mentioning the value of reviewing the other sections, 4) To describe drinking diary cards, 5) To identify a helper, and 6) To mention the 6 and 12 months follow-up assessments.

The Information-Motivation-Behavioural Skills (IMB) Model will be used to guide the alcohol reduction intervention. The IMB model [12-14] proposes that *information *about alcohol misuse and methods of reducing and preventing harmful and/or hazardous drinking is a necessary precursor to risk reduction. *Motivation *to change, however, also directly affects whether one acts on information about risk and risk reduction. Finally, the IMB model holds that *behavioural skills *related to preventive actions represent a final common pathway for information and motivation to result in alcohol risk behaviour change. The IMB model posits that information and motivation activate behavioural skills to ultimately enact risk reduction behaviours. The IMB model also shows that information or motivation alone can have direct effects on some preventive behaviours, such as when information about risky alcohol drinking prompts drinking in moderate levels or to stop drinking.

### Counsellor training and intervention quality assurance

The intervention research assistant counsellor will deliver the interventions to men and women patients as per usual clinic services. There is a comprehensive manual for the brief intervention which will be used to guide the research assistant counsellor throughout the session. The research assistant counsellors will be trained to administer the intervention protocol through role playing and general skills training techniques in a 5 day workshop. Site visits will be done bi-weekly by the project manager to offer support and supervision to the trained research assistant counsellors. In terms of control around the quality and consistency of the implementation of the intervention, research assistants will indicate which intervention was provided to the patient as part of an addition to the AUDIT questionnaire. In addition, research assistants will be able to report to their coordinators regarding any problems they may be having in implementing the brief intervention. Regular meetings between the researchers and the project manager will allow for any problems to be resolved in good time. Prior to intervention implementation, research assistants will be observed in role-play demonstrations until performance criteria are met. In addition, during implementation, research assistants will be observed "in vivo" for adherence to the protocol. Weekly supervision will be provided by a trained counsellor mentor.

#### Outcome measures

##### Demographic characteristics

A researcher-designed questionnaire will be used to record information on participants' age, gender, educational level, marital status, income, and residential status.

##### Health-status

The SF-12 is a multipurpose short-form (SF) generic measure of health status. The SF-12 Health Survey includes 12 questions from the SF-36 [15]. These include: 2 questions concerning physical functioning; 2 questions on role limitations because of physical health problems; 1 question on bodily pain; 1 question on general health perceptions; 1 question on vitality (energy/fatigue); 1 question on social functioning; 2 questions on role limitations because of emotional problems; and 2 questions on general mental health (psychological distress and psychological well-being). In addition, participants will be asked about a list of chronic conditions such as heart disease and diabetes.

##### Alcohol consumption

The 10-item Alcohol Disorder Identification Test (AUDIT) [16] assesses alcohol consumption level (3 items), symptoms of alcohol dependence (3 items), and problems associated with alcohol use (4 items). Responses to items on the AUDIT are rated on a 4-point Likert scale from 0 to 4, with a maximum score of 40 points. AUDIT scores higher than 19 indicate more severe levels of risk; scores of 8-19 in men and 7-19 in women indicate a tendency to problematic drinking. To comply with the timeline of this study, all subjects will be asked for their alcohol consumption in the previous 6 months rather than 1 year.

The primary outcome measure used in this study is the change in drinks per week from baseline to follow-up, as estimated from the first two AUDIT questions. A secondary measure is the frequency of consuming four or more drinks per occasion (AUDIT question 3). The percentage of patients whose weekly consumption decreases, increases, or remains the same, as well as changes in a combination of the first three AUDIT item scores called the Drinkers' index, will also be evaluated in order to estimate the amount of alcohol risk reduction.

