### Sample size calculation

The sample size was calculated using the Protocol Support Tool for Randomize Control Trial Research Software (PST Version 1), for a two arm randomized controlled trial, with 80% power, significance level of 5%, two sided-tests, standard deviation of the control group measurement of 5, and a mean difference between intervention and control of 2. The minimum sample size of each group is 99. To accommodate a drop-out rate of 15% at each follow up, the sample size for each group has been increased to 140, this makes 280 in total.

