### Data analysis

Means, standard deviations, and percentages will be used for descriptive statistics. *T*-test for continuous data and chi-square for categorical data will be used to examine differences between groups. Generalized Linear Model Repeated Measures 2 × 3 Analysis of Variance (ANOVA) will be used for comparing observations (alcohol use score) across the three contact periods to demonstrate a treatment intervention × time interaction. Observations with a single follow-up point missing (at either 6 or 12 months) will be imputed with the available follow-up. Data for participants who are lost to follow-up at both 6 and 12 months will be imputed using baseline values. SPSS for Windows version 17.0 (SPSS, Inc., Chicago, IL) will be used for calculations.

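### Patients lost at both follow-ups are counted as *unchanged* in the decrease / same / increase outcome, and the only categorical test named ignores the order of those categories

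*Protocol article*

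**What the plan says.** The Alcohol consumption section (under Outcome measures) sets a continuous primary outcome: "The primary outcome measure used in this study is the change in drinks per week from baseline to follow-up". After that and one named secondary measure it adds, as a further way to gauge risk reduction, "The percentage of patients whose weekly consumption decreases, increases, or remains the same".

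The Data analysis section contains three rules that bear on this outcome:

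- On testing, it says that "chi-square for categorical data will be used to examine differences between groups". It names no method for ordered categories and does not mention this outcome by name.
- On patients with no follow-up at all: "Data for participants who are lost to follow-up at both 6 and 12 months will be imputed using baseline values".
- On patients with one missed visit: "Observations with a single follow-up point missing (at either 6 or 12 months) will be imputed with the available follow-up".

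The Sample size calculation section plans 140 per arm and allows for 15% drop-out at each follow-up.

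**The concern.** There are two separate issues.

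**Imputation.** If the follow-up value is set equal to the baseline value, the change is zero by construction. The patient can then only fall in the *same* category. The table would mix patients who were seen and had not changed with patients who were never seen again. A reader using the percentages to judge how many patients cut down would be misled about both the *decrease* and the *same* figures. If loss differs between arms, the arms would also differ in *same* for a reason unrelated to drinking.

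**Choice of test.** The categories run from benefit through no change to harm, and the Study hypotheses section expects more reduction in the intervention arm. A 2-df chi-square treats the three categories as unordered labels. It does not target a shift in one direction, and a significant result does not by itself show which way the arms differ.

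**Working it through.** **Inputs from the protocol article.** "80% power, significance level of 5%, two sided-tests"; "standard deviation of the control group measurement of 5"; "a mean difference between intervention and control of 2"; 99 per arm at minimum; 15% drop-out at each follow-up; 140 per arm. The protocol gives no category percentages and no rate of loss at both visits, so those below are assumptions.

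**1. The plan's own figures.** n = 2(1.96 + 0.84)² × 5²/2² = 98.1, so 99 per arm, as stated. For drop-out, 99/0.85² = 137.02, so 138, against the stated 140. There is no dispute here.

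**2. Share lost at both visits (d).** Independent losses: 0.15 × 0.15 = 2.25%, about 3 of 140 per arm. The same patients miss both visits: 15%, or 21 of 140. A patient with one missed visit receives the other follow-up value, which does not force *same*.

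**3. Effect on the reported percentages.** Reported *decrease* and *increase* = true × (1 − d); reported *same* = true × (1 − d) + d. For an assumed 50/30/20%:

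| d | decrease | same | increase |
|---|---|---|---|
| 2.25% | 48.9 | 31.6 | 19.6 |
| 15% | 42.5 | 40.5 | 17.0 |

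(The first row adds to 100.1 by rounding.)

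**4. Equal loss in both arms.** Every group difference is multiplied by (1 − d). Example: control 30/40/30% and a common odds ratio of 2.0 give 46.2/36.2/17.6% in the intervention arm. The true gap in *decrease* of 16.2 points is reported as 15.8 (d = 2.25%) or 13.7 (d = 15%). Type I error stays at 5%. At d = 15%, chi-square power is 72.0% with imputation and 72.4% with the lost patients left out, so almost all of the power loss is the loss of the patients.

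**5. Unequal loss, no true effect.** Assume 10% v 20% lost at both visits (mean 15%, the upper end of step 2), 140 per arm. The noncentrality of the 2-df test is the sum over arms and categories of 140 × (arm proportion − pooled proportion)²/pooled proportion.

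- True split 20/60/20% in both arms: reported 18/64/18 v 16/68/16, pooled 17/66/17. Noncentrality = 280 × (0.01²/0.17 + 0.02²/0.66 + 0.01²/0.17) = 0.50; rejection 9%.
- True split 60/20/20% in both arms: reported 54/28/18 v 48/36/16, pooled 51/32/17. Noncentrality = 280 × (0.03²/0.51 + 0.04²/0.32 + 0.01²/0.17) = 2.06; rejection 23%.
- 30/40/30, 40/35/25 and 50/30/20% lie between: 13%, 15% and 17%.

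On the same five splits a 1-df trend test rejects in 5% to 7%. The false gap in *decrease* is 0.10 × the true percentage, so 2 to 6 points, against the arm with more loss.

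**6. Cost of ignoring order, no loss.** Asymptotic power at 140 per arm, with control splits 30/40/30, 40/35/25 and 20/60/20% and common odds ratios of 1.5 to 2.25. An ordered test (linear trend or Mann-Whitney) gains about 4 to 11 points over chi-square. Examples:

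| Control; odds ratio | chi-square | trend |
|---|---|---|
| 30/40/30; 1.75 | 60.6% | 70.7% |
| 30/40/30; 2.0 | 79.6% | 86.9% |
| 20/60/20; 2.0 | 74.3% | 82.7% |
| 30/40/30; 2.25 | 90.6% | 94.7% |

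A simulation of the second row gave 80.0% for chi-square and 88.0% for Mann-Whitney.

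**7. When order does not help.** Assumed 30/40/30 v 45/25/30%, where patients move only from *same* to *decrease*: chi-square 77%, trend 34%.

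**The case against.** The protocol article never says that this outcome will be tested by chi-square. It gives a one-line general rule, describes these percentages in the language of estimation, and says that percentages serve as descriptive statistics. The imputation sentences follow the one on the repeated-measures ANOVA, so their use here is also an inference. This stands as a limit on certainty. But chi-square is the only test named for categorical data, and the imputation rule is stated for patients' data without restriction, so both inferences are fair.

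A reader might infer that chi-square itself distorts the result. The documents do not support that. The test keeps its 5% error rate when the data are sound, leaves the percentages unchanged, and is the stronger test when the effect is not one-directional (step 7). The direction can also be read from the percentages beside it.

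A reader might also take the artefact to equal the planned 15% loss rate. That figure applies to each visit, and only patients lost at both are set to baseline. The Procedure section plans at least six contact attempts and renewed attempts at 12 months, which should limit double loss. So 15% is the upper end of the range used here.

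Finally, with equal loss the rule is conservative and costs little. That is correct; false positives need unequal loss, which the protocol does not predict. It is possible, since patients are not blinded and controls get a leaflet without screening feedback, but the 10% v 20% is an assumption.

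**Conclusion.** The point holds as a minor one on a supporting outcome. The imputation part follows from the stated rule: each patient lost at both visits would be reported as unchanged. Its size depends on how far the losses at the two visits overlap. It is negligible at 2.25% and visible at 15%, where about one patient in seven in the table was never observed after baseline. The inflated rejection rate arises only if loss differs between arms.

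The test part is a loss of efficiency for the kind of shift that the trial hypothesises, not an error of validity. Its size rests wholly on assumed category splits and a common odds ratio.

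**What to change.** Two sentences in the Data analysis section would do:

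- Tabulate *decrease / same / increase* among patients with an observed follow-up, and show those not followed up in a separate row for each arm.
- Compare the ordered categories by a Mann-Whitney test, a linear trend test or a proportional odds model; the last gives one odds ratio with a direction.

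This needs no new data or patients and leaves the primary analysis as it is. There are two modest costs. Power is lower if the effect is not one-directional (step 7). And percentages among observed patients are fair only if loss is unrelated to the change in drinking, which is why the separate row matters: it lets the reader see how much is unknown in each arm.
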